### Analysis of APCs and FFR_CT_ against an invasive FFR standard

APCs and FFR_CT_ will be assessed against an invasive FFR standard for diagnosis of lesion-specific ischemia. Direct comparison of an integrated APC-FFR_CT_ metric to a non-invasive gold standard by a composite perfusion, MBF, ECG, and functional capacity metric will then be made.

### (A) Assessment of APCs for diagnosis of lesion-specific ischemia

Coronary vessels from 309 patients (927 vessels) with moderate or severe ischemia by MPS and who undergo ICA will be studied, so as to determine the physiologically most relevant APCs. If there is no ischemia in a vessel, then the angiographically most severe lesion measured by invasive FFR will be chosen for APC assessment. For these vessels, associations of the APC measures will be examined in relation to vessel-based ischemia.

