## Methods/Design

The Computed TomogRaphic Evaluation of Atherosclerotic DEtermiNants of Myocardial IsChEmia (CREDENCE) trial (clinicaltrials.gov NCT02173275) is a prospective multicenter cross-sectional study of 618 individuals (*n* = 309 [derivation cohort]; *n* = 309 [validation cohort]) wherein eligible participants will undergo CCTA, MPS, ICA and FFR. For the purposes of the study, either MPS, CCTA, and/or FFR will have been performed for clinical purposes, with the other test being performed as part of the trial procedure. Study analyses will focus on the diagnostic performance of MPS versus CCTA against the gold standard of invasively determined FFR for vessel-specific ischemia.

The relationships of anatomic APCs and physiologic FFR_CT_ by CCTA will be assessed according to measures of vessel-specific ischemia, referenced to an invasive FFR standard. An integrated anatomic-physiologic metric by CCTA for vessel-specific ischemia will be developed from a derivation cohort and tested against a validation cohort, both of which will undergo CCTA, MPS, ICA and FFR. Similarly, an integrated metric by MPS for vessel-specific ischemia will be developed and validated. The performance of this integrated CCTA measure will be directly compared with MPS for diagnosis of vessels that manifest ischemia. The schematic summary of the trial design is depicted in Fig. 1.

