## Target population

The CREDENCE target population will comprise a large and representative sample of individuals for whom CCTA and MPS testing confer the largest potential benefit; that is, for those with suspected CAD who are being referred for non-emergent clinically indicated ICA based upon an imaging study (either MPS or CCTA). In this regard, CREDENCE will enroll adult individuals who meet the inclusion criteria and none of the exclusion criteria, as detailed in Table 1. The study is considered non-significant risk because all subjects will undergo clinically-indicated ICA as planned, with FFR performed in vessel territories with >40 % stenosis for which there is equipoise of ischemia presence [20].

**Table 1 Tab1:** CREDENCE trial inclusion and exclusion criteria

*Inclusion criteria*	
(1) Age ≥18 years	
(2) Patients scheduled to undergo clinically-indicated non-emergent invasive coronary angiography	
*Exclusion criteria*	
(1) Known coronary artery disease (myocardial infarction, percutaneous coronary interventions, coronary artery bypass graft)	
(2) Hemodynamic instability	
(3) Inability to provide written informed consent	
(4) Concomitant participation in another clinical trial in which an individual is subject to investigational drug or device	
(5) Pregnancy or unknown pregnancy status	
(6) Absolute contraindication to iodinated contrast due to prior near-fatal anaphylactoid reaction (laryngospasm, bronchospasm, cardiorespiratory collapse, or equivalent)	
(7) Impaired chronic renal function (serum creatinine ≥1.7 mg/dl or Glomerular Filtration Rate <30 ml/min)	
(8) Baseline irregular heart rhythm (e.g., atrial fibrillation, etc.)	
(9) Heart rate ≥100 beats per minute	
(10) Systolic blood pressure ≤90 mm Hg	
(11) Contraindications to β blockers or nitroglycerin or adenosine	

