### (B) Assessment of FFR_CT_ for diagnosis of lesion-specific ischemia

In individuals who experience ischemia, coronary lesions from 309 patients will be studied, and ischemic vessels will be identified by invasive FFR. The region within the same coronary vessel will be identified distal to the most angiographically obstructive stenosis on the CCTA image that was measured by FFR. The agreement between measured FFR_CT_ and invasive FFR will be examined for these vessels, both as dichotomous (≤ versus >0.80) and continuous (ranging from 0 to 1) variables. In addition, the diagnostic performance of FFR_CT_ to invasive FFR will be tested by measures of sensitivity, specificity, positive predictive value (PPV), and negative predictive value (NPV).

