### (C) Derivation and validation of an integrated anatomic-physiologic CCTA metric for diagnosis of ischemia

An integrated CCTA metric will then be developed that will represent the most parsimonious set of APCs for improving diagnosis of vessel-specific ischemia. The weighted APC set will be combined to FFR_CT_ values using information derived from (A) and (B). Multivariate mixed-effects logistic regression analyses will be conducted with APC-FFR_CT_ measures as a predictor of ischemia. A backward stepwise selection method will be used so that only significant variables at *p* < 0.05 level will be included in the final model. Since these analyses are on a per-vessel basis, a random effects model will be used to account for within-patient clustering. Finally, a summary APC-FFR_CT_ metric as a predictor of ischemia, accounting for the weighted contribution of APCs and FFR_CT_, will be obtained. This summary APC-FFR_CT_ metric will be tested for its ability to diagnose vessel-based ischemia in a validation cohort of 309 patients who will also undergo CCTA, MPS, ICA, and FFR.

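### Sections (A) and (B) restrict the 309 derivation patients to those with ischemia, but enrolment imposes no such condition, so the CCTA metric's derivation population is contradictory

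*Protocol article*

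**What the plan says.** Methods/Design describes a "prospective multicenter cross-sectional study of 618 individuals", split into 309 for derivation and 309 for validation. The integrated CCTA metric "will be developed from a derivation cohort and tested against a validation cohort, both of which will undergo CCTA, MPS, ICA and FFR". One or more of the tests will have been done clinically, "with the other test being performed as part of the trial procedure", so MPS may be a study procedure.

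Table 1 (Target population) has two inclusion criteria: adult age and "Patients scheduled to undergo clinically-indicated non-emergent invasive coronary angiography". None of the eleven exclusions refers to an MPS result or to ischemia. The text above the table allows the referral to rest on either MPS or CCTA.

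The analysis sections describe a narrower group:

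- (A), which selects the APCs: "Coronary vessels from 309 patients (927 vessels) with moderate or severe ischemia by MPS and who undergo ICA will be studied".
- (B), which assesses FFRCT agreement, sensitivity, specificity, PPV and NPV: "In individuals who experience ischemia, coronary lesions from 309 patients will be studied, and ischemic vessels will be identified by invasive FFR".

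Section (C) combines the weighted APC set with FFRCT using what (A) and (B) yield, and tests the result in "a validation cohort of 309 patients who will also undergo CCTA, MPS, ICA, and FFR". No ischemia condition is attached to that cohort.

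**The concern.** The number 309 is used both for the whole derivation cohort and for a subset of it defined by a test result. Someone enrolled on a CCTA referral, with MPS then done for the trial, may have a normal or mildly abnormal MPS. That patient is eligible under Table 1 but does not fit (A).

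An analyst who follows (A) and (B) literally would drop such patients and miss the stated 309 and 927. An analyst who follows Methods/Design and Table 1 would keep them and depart from (A) and (B). The article does not say which is meant.

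Under the literal reading, APC selection, weights and calibration come from patients selected on MPS, which is the comparator test. The FFRCT part comes from patients selected on ischemia. Section (B) does not name the test that defines ischemia. Its sentence goes on to identify ischemic vessels by invasive FFR, so selection on the reference standard is the natural reading. If MPS is meant, it is selection on the comparator again. Either way, the metric is then tested in patients who are not described as selected, and the predictive values in (B) would not describe the stated target population.

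**Working it through.** **1. The plan's own counts.** 618 / 2 = 309 patients per cohort (Methods/Design). 309 × 3 territories = 927 vessels, as stated in (A). The restricted set in (A) is therefore exactly as large as the full derivation cohort.

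**2. When both statements can hold.** Let f be the share of enrolled patients with moderate or severe MPS ischemia. Patients available to (A) = 309 × f, which equals 309 only at f = 100 %. The article gives no f, so a range is assumed:

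| f (assumed) | Patients of 309 | Vessels (× 3) | Derivation enrolment needed for 309 (309 / f) |
|---|---|---|---|
| 50 % | about 154 | 462 | 618 |
| 70 % | about 216 | 648 | 442 |
| 80 % | about 247 | 741 | 387 |

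**3. Drawing the 309 from all 618 does not rescue it.** At f = 50 %, 618 × 0.5 = 309, so every such patient goes to derivation and none is left for validation. At f = 70 %, 618 × 0.7 ≈ 433, and 433 − 309 = 124 remain, or 124 / 309 ≈ 40 % of the validation cohort against 100 % of the derivation cohort. The count is met, but the two cohorts then differ in spectrum by construction.

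**4. Starting prevalence for FFRCT.** The Discussion cites per-vessel FFRCT figures from DISCOVER-FLOW: sensitivity (Se) 87.9 %, specificity (Sp) 82.2 %, PPV 73.9 %, NPV 92.2 %. The implied vessel prevalence p follows from PPV/(1 − PPV) = [Se/(1 − Sp)] × p/(1 − p):

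- 0.739/0.261 = 2.831 and 0.879/0.178 = 4.938
- p/(1 − p) = 2.831/4.938 = 0.573, so p ≈ 0.364

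Check: NPV = 0.822 × 0.636 / (0.822 × 0.636 + 0.121 × 0.364) = 0.92, as cited.

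**5. Rise in prevalence from selection on ischemia.** A simulation with three vessels per patient and an assumed patient random effect (logit SD 1.0) kept only patients with at least one FFR-ischemic vessel. Vessel prevalence rose from 0.205 to 0.457, from 0.306 to 0.510 and from 0.404 to 0.562, which are gains of about 0.25, 0.20 and 0.16. Adding 0.16 to 0.25 to 0.36 gives 0.52 to 0.61. The gain shrinks as the starting prevalence rises. Interpolating between the last two rows at 0.364 gives 0.204 − 0.046 × (0.058/0.098) ≈ 0.18, or a prevalence near 0.54. The upper end of 0.61 is therefore an outer value.

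**6. Effect on predictive values, with Se and Sp held fixed.** PPV = Se·p / [Se·p + (1 − Sp)(1 − p)]. NPV = Sp(1 − p) / [Sp(1 − p) + (1 − Se)p].

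| Prevalence | PPV | NPV |
|---|---|---|
| 0.364 | 0.74 | 0.92 |
| 0.52 | 0.457/(0.457 + 0.085) = 0.84 | 0.395/(0.395 + 0.063) = 0.86 |
| 0.54 | 0.475/(0.475 + 0.082) = 0.85 | 0.378/(0.378 + 0.065) = 0.85 |
| 0.61 | 0.536/(0.536 + 0.069) = 0.89 | 0.321/(0.321 + 0.074) = 0.81 |

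**The case against.** The strongest reply is that the two phrases are loose wording, that (A) never says it describes the derivation cohort, and that the main comparison is untouched.

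The first part does not dispose of the point. The identical 309, and the statement in (C) that the metric is built from (A) and (B), tie both sections to derivation, and nothing elsewhere in the article removes the restriction.

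The rest of the reply limits what can be claimed. A reader might infer that both integrated metrics are derived in the restricted group, that the MPS metric suffers most because its own predictor range is cut, and that the head-to-head is therefore tilted. The documents do not support this, for these reasons:

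- Methods/Design says only that the MPS metric is developed in a similar way. Its derivation set is not stated.
- Section (D) makes the comparison in the validation cohort, which carries no stated restriction. Selecting on a positive MPS raised apparent MPS sensitivity by about 0.06-0.13 and lowered specificity by about 0.07-0.15 in simulations with assumed inputs. Those would be derivation-set figures, which the plan does not compare.
- The MPS section gives a fixed definition of an inducible perfusion abnormality, so a perfusion-only comparator needs no derived cut-off.
- If only the CCTA metric is derived in the selected group, CCTA is the arm put at risk. The Background also notes that selected APCs are associated with MPS ischemia, so CCTA measures cannot be assumed unaffected by selection on MPS.

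Nor is it right to say that the predictive values in (B) are computed only in diseased units. Non-ischemic vessels stay in as controls, and (A) provides for them. Specificity can still be estimated, in a selected spectrum.

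**Conclusion.** The contradiction holds and needs no assumption: the 309 patients and 927 vessels in (A), and the 309 patients in (B), match the enrolled derivation cohort only if every patient in it is ischemic, and the eligibility criteria do not require that.

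The consequence that can be supported concerns the CCTA metric. Read literally, its APC selection, weights and calibration would come from a spectrum selected on the comparator or on the outcome, and would then be tested in a cohort not so described. The size of that effect on the metric has not been quantified.

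The two figures that can be offered both rest on assumptions. The count of about 154 to 247 qualifying patients depends on an assumed MPS-ischemic share of 50 to 80 %. The shift in FFRCT predictive values (PPV 0.74 to 0.84-0.89, NPV 0.92 to 0.86-0.81) depends on three assumptions: that ischemia in (B) means invasive FFR, that the cited sensitivity and specificity carry over unchanged, and that prevalence rises as simulated. It affects a component analysis, not the primary comparison. No direction of bias in the validation-cohort comparison of CCTA with MPS has been shown.

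This is a rule stated wrongly, not detail left to another document, and it should be settled before derivation begins.

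**What to change.** State one derivation population, consistent with Table 1 and with the validation cohort. In (A), remove the qualifier requiring moderate or severe ischemia by MPS. In (B), remove the opening restriction to individuals with ischemia. All 309 derivation patients then enter (A) to (C), and the figures 309 and 927 stand as printed. Keep the need for an ischemic and a non-ischemic vessel only in the two within-subject matched comparisons, where the pairing requires it.

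If the restriction is truly intended, state it as an eligibility condition for both cohorts, name the test that defines ischemia in (B), and restate the target population and the 309 and 927 counts to match.

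The first option is a wording change in two sections, with no added patients or tests. The second could raise enrolment: at the assumed shares of 50 to 80 %, 618 down to 387 patients would have to be enrolled to yield 309 for derivation alone, and the same again for validation.

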### Within-subject comparison of APCs of ischemia-causing versus non ischemia-causing coronary lesions

APCs within ischemia-causing lesions will be compared with within-subject control lesions. Matched analysis will be performed to predict the likelihood of a vessel being ischemic based on APCs for lesions (e.g., matched 1:1 within persons); with an ischemic vessel––that possess the angiographically most severe stenosis and is measured by invasive FFR––matched to one of the remaining arteries (LAD, LCx or RCA).

Moreover, additional ischemic:nonischemic vessel combinations will be considered. For any patient with one ischemic vessel, an analysis will be performed using a 1:2 case:control match to compare results with the 1:1 matched analysis. For individuals with two ischemic vessels, a 2:1 case:control match will be performed for each ischemic vessel to the same non-ischemic control vessel, and then comparing these results with the 1:1 matched analysis.

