### Within-subject comparison of FFR_CT_ of ischemia-causing lesions to non-ischemia causing coronary lesions

FFR_CT_ for ischemic vessels will be compared with within-subject controls. Matched analysis will be performed to predict the likelihood of a vessel to be ischemic based on FFR_CT_ for lesions matched 1:1 within a person. Within-subject matched comparisons will be performed as discussed earlier for the APCs.

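### The 1:1 within-patient match takes the most stenotic ischemic vessel and one unspecified control, which wastes usable vessels and can inflate odds ratios; one m:n conditional model avoids both

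*Protocol article*

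**What the plan says.** Protocol article, section (A), describes the derivation pool: "Coronary vessels from 309 patients (927 vessels) with moderate or severe ischemia by MPS and who undergo ICA will be studied". Its within-subject subsection then states the aim, "Matched analysis will be performed to predict the likelihood of a vessel being ischemic based on APCs for lesions", with the ratio given as an example ("e.g., matched 1:1 within persons"). The case is an ischemic vessel that has the angiographically worst stenosis and an invasive FFR. It is "matched to one of the remaining arteries (LAD, LCx or RCA"), with no rule for which one.

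Two further analyses follow: "For any patient with one ischemic vessel, an analysis will be performed using a 1:2 case:control match", and a 2:1 set when two vessels are ischemic. Each is to be compared with the 1:1 result.

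The within-subject subsection of (B) repeats the scheme for FFR_CT, "Matched analysis will be performed to predict the likelihood of a vessel to be ischemic based on FFR_CT_ for lesions matched 1:1 within a person", and refers back to the procedure for plaque characteristics (APCs).

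Section (C) says: "The weighted APC set will be combined to FFR_CT_ values using information derived from (A) and (B"). It then specifies a per-vessel mixed-effects logistic regression with random effects for patients, backward selection at p < 0.05, and a summary metric to be tested in the validation cohort.

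**The concern.** A patient has at most three territories, so usable within-patient information is limited. A 1:1 base analysis takes two vessels from each eligible patient even when all three have an FFR class. The 1:2 and 2:1 runs bring the third vessel back, but separately for patients with one and with two ischemic vessels. No planned estimate combines them.

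The choice of case is a second problem. When two vessels are ischemic, taking the more stenotic one selects on a variable related to most of the listed APCs and to FFR_CT. The selected case then has a more extreme value than a typical ischemic vessel, while the control is not selected in the same way. The odds ratio rises for that reason alone.

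Third, the stated aim of predicting a likelihood does not match what a within-patient match can estimate.

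At stake are the size and precision of the APC and FFR_CT associations that indicate which APCs matter most. The primary accuracy comparison does not rest directly on the matched analyses.

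**Working it through.** **Pool.** 309 patients × 3 territories = 927 vessels, which reproduces the article's figure. The article gives neither the per-vessel prevalence of FFR ≤ 0.80 nor the between-patient spread, so everything below is assumption-dependent.

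**1. Who contributes.** A matched set needs at least one ischemic and one non-ischemic vessel.

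Share = 1 − P(none ischemic) − P(all three ischemic).

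- Independent vessels, prevalence 25 %: 1 − 0.75³ − 0.25³ = 1 − 0.422 − 0.016 = 0.563, or 174 of 309.
- Independent vessels, prevalence 50 %: 1 − 0.125 − 0.125 = 0.75, or 232.
- Patient-effect SD 2 on the logit scale, prevalence 15 %: 0.26, or 80.

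Across prevalence 15 to 50 % and SD 0 to 2 the range is 26 to 75 % (80 to 232 patients). A 1:1 match uses 2 × 80 = 160 to 2 × 232 = 464 vessels. An m:n analysis uses 3 × 80 = 240 to 3 × 232 = 696. These counts assume an FFR class for all three vessels. The article generally limits FFR to stenoses of 40 to 90 %, so measured sets may be fewer.

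**2. Precision.** Simulations used 309 patients, OR 2.0 per SD of the predictor (log OR 0.693), patient SD 1 and assumed prevalence. They compared one m:n conditional fit with the 1:1 fit:

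- SD of the log OR 0.111 against 0.131: (0.111/0.131)² = 0.72, so 28 % less variance.
- SD 0.119 against 0.144: (0.119/0.144)² = 0.68, so 32 % less.
- A third run gave 34 % less.

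As information, this is 1/0.72 = 1.39 to 1/0.66 = 1.52 times that of the 1:1 analysis.

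**3. Effect of picking the case by severity.** A stenosis score was given an assumed correlation of 0.5 to 0.8 with the APC, and the case was the more stenotic ischemic vessel. One simulation gave a 1:1 log OR of 0.76 to 0.83 against 0.66 for m:n, a gap of 0.10 to 0.17. As odds ratios, that is exp(0.76) = 2.14 to exp(0.83) = 2.29 against exp(0.66) = 1.93.

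I repeated this with 1,500 runs per setting, intercept −1.1 (prevalence about 30 %, 54 % of patients forming a set), and stenosis having no effect of its own on ischemia given the APC:

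| Analysis | Mean log OR (true 0.693) |
|---|---|
| 1:1, case chosen at random | 0.70 |
| 1:1, most stenotic case, correlation 0.5 | 0.81 |
| 1:1, most stenotic case, correlation 0.8 | 0.88 |
| m:n, all vessels | 0.70 |

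The gap is 0.11 to 0.18. It widens as prevalence rises, because more patients have two ischemic vessels: at correlation 0.8 it was about 0.12 at 17 % prevalence and about 0.22 at 40 %. With a random case the 1:1 estimate is essentially unbiased, so the excess comes from the selection and not from matching.

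**4. Likelihood.** Write logit P(ischemic) = a + u + b·x, with u the patient effect. Given one case and one control in a patient, the probability that vessel 1 is the case is 1/(1 + exp(−b(x₁ − x₂))); a and u cancel. Simulated populations with a = −2.0 and −0.5 had prevalences of 17.0 % and 40.6 %. The 1:1 fits gave slopes of 0.62 and 0.74 and no intercept. At x = u = 0 the true risks are 1/(1 + e^2.0) = 0.12 and 1/(1 + e^0.5) = 0.38, which the matched fit cannot distinguish. A mixed-effects logistic fit recovered intercepts of −1.99 and −0.49.

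**The case against.** A reader might infer that matched coefficients, which lack an intercept and come only from patients with both kinds of vessel, become the metric's weights. The documents do not support that. The sentence in (C) about information from (A) and (B) is followed by a per-vessel mixed-effects logistic model, which has an intercept and can keep patients with no or only ischemic vessels. The summary metric is introduced after that model. Section (A) also contains an unmatched vessel-level association analysis, and (B) contains agreement and accuracy measures. Information from (A) and (B) can therefore mean simply which APCs look relevant. No passage says that matched coefficients are carried forward.

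It can also be said that 1:1 is only an example, and that the 1:2 and 2:1 sets cover every mixed pattern in a three-vessel patient. That is true as far as use of the vessels goes. But those sets are separate runs set against the 1:1 result. They share cases and controls with it, so their agreement is not independent confirmation, and none yields a pooled estimate.

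Further, restriction to patients with both kinds of vessel does not itself bias the slope under a random-intercept model. That stands; the random-case result above agrees. The bias shown arises only from choosing the case by severity.

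Finally, the subsections are headed as within-subject comparisons, so the likelihood wording may just be loose. Conditional logistic regression is nowhere named; its use here is inferred from the matching. I accept that this part is mostly wording.

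**Conclusion.** The point holds for the design of the within-subject analyses. Relative to the 1:1 base analysis, one m:n conditional model gives roughly 28 to 34 % less variance. It also removes an upward shift of about 0.1 to 0.2 on the log-odds scale for predictors correlated 0.5 to 0.8 with stenosis. Both figures rest on assumed prevalence, an OR of 2.0, a patient SD of 1 and three FFR-classified vessels per patient; the shift also rests on the assumed correlation. The share of patients forming a set is about 26 to 75 %, and the documents do not allow a narrower figure. The estimates are within-patient odds ratios and should not be called likelihoods. The matched analyses are supporting ones, and section (C) as written does not make them the source of the metric's weights.

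**What to change.** In the within-subject subsections of (A) and (B), replace the 1:1, 1:2 and 2:1 runs with one m:n conditional logistic regression. It should use all FFR-classified vessels of patients who have both ischemic and non-ischemic vessels. Describe its result as a within-patient association (odds ratio), and drop the wording about predicting likelihood and the selection of the case by stenosis severity.

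In section (C), keep the mixed-effects all-vessel model as stated. Add one sentence: the weights and intercept of the metric come from that model, and (A) and (B) inform only which APCs are candidates.

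The cost is a few sentences and one model in place of three, with no new data and no change to the sample size.
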